#### Research reimbursement

Male and female participants will be reimbursed in cash or vouchers for their time for completing baseline or follow-up interviews (£10) and taking part in focus groups or qualitative interviews (£20). All research participants will receive £5 travel expenses for attending a research interview.

#### Sample size calculation

The sample size for a feasibility study should allow parameters required to inform the design of the definitive randomised controlled trial to be estimated. To estimate a standard deviation for a sample size calculation of a future evaluation trial, a sample of at least 50 participants is recommended [68]. Therefore, to recruit a sample size of 60 female current or former partners (i.e. 30 whose current or ex male partners in the intervention arm and 30 whose partners are in the control arm), and taking a conservative retention rate of 80% of female current or former partners at end of intervention assessment (4 months post-randomisation), we will recruit 76 female current or former partners. It is estimated that around 70% of current or former female partners will agree to take part in the trial, therefore approximately 108 male participants will need to be recruited to obtain a sample of 76 female current or former partners.

#### Statistical analysis

This feasibility trial will estimate parameters needed for planning an efficacy trial including estimating various rates (e.g. recruitment, randomisation, follow-rates) and estimating the within-trial arm standard deviation, the pre-post correlation, and the Intracluster Correlation Coefficient (*ICC*) for possible outcome measures to inform the sample size calculation of a future randomised control trial. Outcome measures will be rated by the researcher for each participant for their suitability and acceptability and the mean scores summarised for each outcome. Outcome measures will be described by trial arm. Intervention effect sizes (e.g. incidence rate ratios for the count outcome and mean differences for continuous outcome measures) will be estimated for various outcome measures, but no formal hypotheses testing will be carried out.

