### Participant-centred outcome measures

The suitability and acceptability of outcome measures will be assessed to determine the feasibility of including them in a future effectiveness trial. Researchers’ perceptions of participants’ understanding (e.g. of language and meaning of questions) and acceptability (e.g. if participant refuses to answer or gets annoyed/frustrated or asks to end the interview) will be recorded for each outcome measure using a pre-determined rating scale (1—lowest rating to 3—highest rating for understanding and acceptability). The following outcome measures will be assessed at baseline for men and initial interview for women and at the end of the intervention (4 months post-randomisation of men) for men in both treatment arms and their current or former female partners (unless otherwise specified) (Table 2).

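### The three-point ratings of each outcome measure are summarised by a mean, which does not show how many participants received the lowest rating

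*Protocol article*

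**What the plan says.** The section on participant-centred outcome measures gives the purpose: "The suitability and acceptability of outcome measures will be assessed to determine the feasibility of including them in a future effectiveness trial". The researcher's impression is recorded for each measure on a "pre-determined rating scale (1—lowest rating to 3—highest rating for understanding and acceptability". The examples given for acceptability are events during the interview: "if participant refuses to answer or gets annoyed/frustrated or asks to end the interview".

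The Statistical analysis section repeats the unit of rating, "Outcome measures will be rated by the researcher for each participant for their suitability and acceptability", and then names the summary: "the mean scores summarised for each outcome". It names no other summary of these ratings. It mentions no split between men and women or between baseline and follow-up at this point.

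**The concern.** The score is ordinal with three levels. For choosing measures, the low end is the informative part: a measure that a minority reject outright is a different problem from one that some participants find middling and nobody rejects. A mean can be the same for both.

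The first pattern is plausible here, because the instruments ask about physical, sexual and psychological abuse, stalking and the use of children against a partner. Most participants may answer readily while a few object strongly. What is at stake is how well the feasibility trial can inform the choice of measures for the next trial. No effect estimate and no safety matter depends on it.

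The groups also differ. The abuse measures cover both perpetration and victimisation, men and women are recruited in different numbers, and several instruments go to men only (for example the responsibility attribution scale, the anger subscale and the self-control scale). If the ratings of a shared measure were pooled, the men's would carry more weight, although the sample size is built on the women.

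**Working it through.** **Inputs from the protocol article.** The scale runs from 1 to 3 (Participant-centred outcome measures). The sample size section gives about 108 men, 76 women recruited and 60 women at follow-up, with 80% retention and 70% uptake. These numbers serve here only as denominators.

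**The article's own figures.** 60 / 0.80 = 75, against 76 stated. 76 / 0.70 = 108.6, against approximately 108 stated, and 108 × 0.70 = 75.6. The stated figures are reproduced to within rounding and are not in dispute.

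**What a mean fixes.** Let p1, p2 and p3 be the shares rated 1, 2 and 3, with p1 + p2 + p3 = 1. Then

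m = p1 + 2·p2 + 3·p3 = 2 + p3 − p1.

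So the mean fixes only the difference p3 − p1. Substituting p3 = m − 2 + p1 gives p2 = 3 − m − 2·p1. This must not be negative, so for m of 2 or more

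0 ≤ p1 ≤ (3 − m) / 2.

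**Assumed examples** (the article gives no ratings and no threshold):

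- 10% rated 1 and 90% rated 3: 0.10 × 1 + 0.90 × 3 = 2.8.
- 20% rated 2 and 80% rated 3: 0.20 × 2 + 0.80 × 3 = 2.8.
- 25% rated 1 and 75% rated 3: 0.25 × 1 + 0.75 × 3 = 2.5.
- 50% rated 2 and 50% rated 3: 0.50 × 2 + 0.50 × 3 = 2.5.

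In 60 women, the first two patterns are 6 lowest ratings (10%, exact 95% CI 3.8% to 20.5%) and none (0% to 6.0%), with the same mean.

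**Range of lowest ratings compatible with a given mean**, found by listing all whole-number counts (means are approximate where n × m is not a whole number):

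| Mean | 60 women | 76 women | 108 men |
|---|---|---|---|
| 2.8 | 0 to 6 (10.0%) | 0 to 7 (9.2%) | 0 to 11 (10.2%) |
| 2.6 | 0 to 12 (20.0%) | 0 to 15 (19.7%) | 0 to 21 (19.4%) |
| 2.5 | 0 to 15 (25.0%) | 0 to 19 (25.0%) | 0 to 27 (25.0%) |
| 2.2 | 0 to 24 (40.0%) | 0 to 30 (39.5%) | 0 to 43 (39.8%) |

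**Pooling.** If a measure were rated once for all 108 men and 76 women, the men would supply 108 / (108 + 76) = 58.7% of the ratings.

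**The case against.** The strongest reply is that one descriptive sentence in a condensed article is being asked to carry too much. The article does not say that the mean is the only summary, and category counts could sit beside it. Its list of rates is open, "estimating various rates (e.g. recruitment, randomisation, follow-rates", and collecting outcome measures from men and women is itself part of the primary objective. An analysis plan that is not shown may add completion rates. All of this stands, so the point rests on the statistic that the article does name and not on anything it leaves out.

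Three stronger readings are tempting, and the document supports none of them.

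- **That measures will be kept or dropped on their mean.** The ratings inform feasibility, but the article gives no threshold, ranking or retention rule.
- **That the mean conceals refusals or non-completion.** Refusing, being annoyed and asking to stop are only examples of what bears on acceptability. No text equates a rating of 1 with refusal, and a participant who was annoyed but answered everything could also score low. Refused or missing measures can be counted whatever summary is used for the rating.
- **That the lowest rating predicts missing outcome data.** Nothing in the article shows this.

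The ratings are also one researcher's judgement, and researchers are not blind to allocation. That is a reason not to build a decision rule on them. It is no argument for a mean over counts.

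**Conclusion.** The point holds as a minor improvement. The named summary is a mean of a three-level ordinal rating, and for any mean of 2 or more it leaves the share at the lowest rating open between 0 and (3 − m) / 2. At 2.5 that is 0% to 25%.

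The algebra needs no assumption, but the particular means and splits are illustrations. How much the choice matters in practice depends on the ratings obtained: if nearly all are 3, the mean and the counts say much the same. Even the share rated 1 is only a proxy for refusal, so refusals need a count of their own.

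**What to change.** Replace the phrase on mean scores with wording such as: *For each outcome measure, the number and percentage of participants at each rating (1, 2, 3) will be reported for understanding and for acceptability, separately for men and women and by time point, alongside the number for whom the measure was refused or missing. Mean ratings may be given as a secondary summary.*

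No retention rule needs to be added. The ratings are already planned per participant and per measure, and refused or missing measures can be counted from the collected questionnaires. The cost is one sentence and a different table layout, with no change to sample size, visits or burden on participants.

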#### Economic analysis

The costs of providing the intervention will be collected from local data sources to estimate the incremental cost of delivering the ADVANCE intervention over and above substance use TAU. Questionnaires on the use of primary and secondary health and social care services and contacts with criminal justice services by men (and their female current or ex-partners) in the intervention and control groups will record quantities of resource use. This resource use will be multiplied by unit costs to estimate a cost profile for each participant. The returned questionnaires will be analysed to assess the acceptability of data collection methods, identify barriers to data collection and highlight the most commonly used services in this population. A more appropriate questionnaire for an efficacy trial can be developed based on the feasibility trial data. A cost profile will be estimated for each participant, including trial-related costs and wider service use costs and presented by treatment arm.

#### Qualitative analysis

Focus groups and semi-structured interviews will be digitally recorded and transcribed verbatim. Data will be organised and coded using NVivo. Multiple coders will enhance the rigour of the analysis. Framework analysis will be used for qualitative data analysis using five steps: familiarization; identifying a thematic framework; indexing; charting; and mapping and interpretation [69]. Collecting multiple perspectives data (e.g. from male and female participants, keyworkers, intervention facilitators, and women’s support staff) in a qualitative formative evaluation will provide a better understanding of the intervention’s implementation. The *framework* approach allows the exploration of patterns in themes across different participants and groups of participants.

#### Data management

In accordance with the Trial Terms of Reference, the Data Monitoring and Ethics Committee will periodically review overall safety data to determine patterns and trends of events, or to identify safety issues, which would not be apparent on an individual case basis and report their findings to the Trial Steering Committee who will provide overall supervision of the feasibility trial.

#### Data handling and storage

Participants’ contact details will be stored on a secure password protected server for 3–6 months after the study has ended. Consent forms will be stored at each site in a locked cabinet and will not contain the participant identification number. Paper copies of questionnaires will be stored separately from the consent forms and contain only a participant identification number. A unique identification code will be assigned to electronic sound files and transcripts of the focus groups, known only to appropriate members of the research team. Any personal information required will also be coded with this identification number and kept in a password protected server. Audio files will not contain participant’s names and will not be stored on the recording device. Audio files will be downloaded onto a secure server. As soon as the audio file is checked on the server, it will be deleted from the recording device. Any quotes published will be anonymous further protecting participant confidentiality. Recordings will be archived in a secure location for a minimum period of 7 years.

## Discussion

IPA remains a leading contributor to disease burden [70]. It is estimated that the annual cost of domestic abuse in England and Wales is over £66 billion, mainly due to the cost of physical and emotional harms experienced by victims/survivors (£47 billion) [71]. There is a need to find effective interventions to reduce IPA perpetration, especially amongst high-risk groups such as substance users. Current provision of community perpetrator groups does not meet demand nor is it tailored to the specific needs of men in substance use treatment. This unmet need led to the development of the ADVANCE intervention. It is hoped that delivering tailored IPA interventions in substance use treatment will increase their ability to reach men who may not otherwise be referred to perpetrator interventions and result in better outcomes for male perpetrators and improved wellbeing for their female partners.

This feasibility trial, and nested formative evaluation, will inform the design of a future trial to evaluate the clinical efficacy and cost-effectiveness trial.

### Trial status

The trial sponsor is South London and Maudsley NHS Foundation Trust. The screening began on 5 July 2018, with the first male participant randomised on 17 July 2018. Recruitment will end on 7 May 2019.

## Data Availability

Not applicable.

## Abbreviations

ADVANCE: Advancing theory and treatment approaches for males in substance misuse treatment who perpetrate intimate partner violence
GDPR: General Data Protection Regulation
IPA: Intimate partner abuse
IPV: Intimate partner violence
ISS: Integrated safety service
RCT: Randomised controlled trial
SPIRIT: The Standard Protocol Items: Recommendations for Interventional Trials
TAU: Treatment as usual
